## Abstract

**Background:**

The spleen plays a significant role in the clearance of circulating microorganisms. Sequelae of splenectomy, especially immunodeficiency, can have a deleterious effect on a patient’s health and even lead to death. Hence, splenectomy should be avoided and spleen preservation during elective surgery has become a treatment goal. However, this cannot be achieved in every patient due to intraoperative technical difficulties or oncological reasons. Autogenic splenic implantation (ASI) is currently the only possible way to preserve splenic function when a splenectomy is necessary. Experience largely stems from trauma patients with a splenic rupture. Splenic immune function can be measured by the body’s clearing capacity of encapsulated bacteria. The aim of this study is to assess the splenic immune function after ASI was performed during minimally invasive (laparoscopic or robotic) distal pancreatectomy with splenectomy.

**Methods:**

This is the protocol for a multicentre, randomized, open-labelled trial. Thirty participants with benign or low-grade malignant lesions of the distal pancreas requiring minimally invasive distal pancreatectomy and splenectomy will be allocated to either additional intraoperative ASI (intervention) or no further intervention (control). An additional 15 patients who will undergo spleen-preserving distal pancreatectomy serve as the control group with normal splenic function. Six months postoperatively, after assumed restoration of splenic function, patients will be given a *Salmonella typhi* (Typhim Vi™) vaccine. The *Salmonella typhi* vaccine is a polysaccharide vaccine. The specific antibody titres immediately before and 4 to 6 weeks after vaccination will be measured. The ratio between pre- and post-vaccination antibody count is the primary outcome measure and secondary outcome measures include intraoperative details, length of hospital stay, 30-day mortality and morbidity.

**Discussion:**

This study will investigate the splenic immune function of patients who undergo ASI during minimally invasive distal pancreatectomy with splenectomy. The splenic immune function will be measured using the surrogate outcome of specific antibody titre after vaccination with a *Salmonella typhi* vaccine. The results will reveal details about splenic function after ASI and guide further treatment options for patients when a splenectomy cannot be avoided. It might eventually lead to a new standard of care making sometimes more demanding and time-consuming spleen-preserving procedures redundant.

**Trial registration:**

International Standard Randomized Controlled Trials Number (ISRCTN) ISRCTN10171587. Prospectively registered on 18 February 2019.

**Supplementary Information:**

The online version contains supplementary material available at 10.1186/s13063-023-07714-1.

## Background

The spleen initiates immune responses to blood-borne antigens, produces antibodies, and clears antibody-mediated pathogens. Some bacteria, in particular encapsulated bacteria, require opsonization to facilitate phagocytosis. In this case, memory B cells located in the spleen produce immunoglobulin M (IgM) that acts as an opsonin to enable the clearance of the polysaccharide-encapsulated bacteria like *Streptococcus pneumoniae*, *Neisseria meningitides*, *Haemophilus influenza* and *Streptococcus pyogenes* [1, 2]. Therefore, splenectomised individuals, with less memory B cells, are at lifelong risk of developing severe septic complications, which can potentially result in “overwhelming post-splenectomy infection (OPSI) syndrome” [3, 4]. While OPSI is relatively rare, with an incidence rate amongst splenectomised individuals of 0.13 per 100 person-years, it can rapidly progress from a mild flu-like illness to a fulminant sepsis with high mortality [4–6]. Due to this increased risk, splenectomised patients require regular vaccinations and, depending on national guidelines, a temporary or permanent commitment to prophylactic antibiotics [7].

Another role of the spleen is hemofiltration, maintaining the morphology and function of red blood cells by removing senescent and altered erythrocytes and particles such as Howell–Jolly bodies (HJB) [8–10]. In fact, a plethora of vascular complications have been described after splenectomy. They mostly arise due to an obstruction of blood vessels as a result of thrombocyte activation, hypercoagulability and a longer life span of erythrocytes and are more pronounced amongst patients with underlying haematological disease [11]. Furthermore, in 985 patients who underwent a splenectomy in conjunction with surgery for non-traumatic or non-malignant conditions of adjacent organs, a 40% increased risk of cancer was found 5–9 years later, with a significantly increased incidence of lung and ovarian cancer [12]. In addition, higher risks of head and neck cancer, digestive tract cancer and haematological malignancies have been reported [13, 14]. In contrast, other studies showed a lower incidence of cancer after splenectomy [15]. In fact, many cancers have been correlated with immunodeficiency, and the spleen plays an obvious role in the immune response. However, these processes are not yet entirely understood. To summarize, the spleen plays a relevant role in the body and, although barely understood, it is clear that splenic preservation is preferred.

Distal pancreatectomy (DP) often comes with concomitant splenectomy (DPS), as a result of the spleen having anatomical proximity to and sharing principal vessels with the body and tail of the pancreas. Furthermore, in the case of a malignancy, splenectomy is routinely performed for oncological reasons. For benign or low-grade malignant lesions such as mucinous cystic neoplasm (MCN), intraductal papillary mucinous neoplasm (IPMN), pseudocyst or chronic pancreatitis, splenectomy has no clear advantages and is associated with greater morbidity [16].

Interestingly, studies comparing the risk of severe post-splenectomy infection showed that rates of infection were lowest amongst patients who underwent a splenectomy because of splenic rupture [5, 17, 18]. This could be explained by spontaneous splenosis, which has been shown to occur in up to 65% of patients who underwent splenectomy for trauma. The phenomenon of spontaneous splenosis is presumed to be caused by seeding of splenic tissue after rupture of the capsule as a consequence of the trauma [19].

With this background, spleen preservation has become the goal in DP for benign conditions and neoplasms with low malignant potential [20]. However, if splenectomy is inevitable, autogenic splenic implantation (ASI) is a potential way to restore splenic function. During this procedure, pieces of splenic parenchyma are placed in the abdominal cavity, mostly in a surgically created pouch of the greater omentum. This results in regeneration of the splenic tissue, most likely as a result of the rich blood supply of the omentum [21, 22]. Multiple series of ASI have been described in the literature, the majority performed after splenectomy in trauma patients. These series have demonstrated that this procedure is safe and feasible with very few complications being reported [23].

Nevertheless, it remains unclear if ASI restores the splenic function, mainly due to difficulties to accurately test the splenic function. Spleen scintigraphy using technetium 99-m labelled erythrocytes or sulphur colloid verifies the presence, volume and perfusion of splenic tissue [24]. An actual qualitative statement about splenic function, however, is not possible. Assessment of blood films for the presence of HJB or pitted red blood cells is another measure reflecting phagocytic capacity. Nevertheless, the relation of the presence of HJB and splenic function remains unclear and morphological assessment is not sensitive [25, 26]. Lastly, experimental animal studies have suggested ASI might restore defects in the immune system of splenectomised individuals [22, 27, 28]. Therefore, the clearance of polysaccharide-encapsulated bacteria, the clinically most relevant function, has been used to assess immune function in humans. One way to measure clearance is by measuring specific antibodies against encapsulated bacteria. These enable opsonisation of bacterial capsules so that immune cells can recognize and attack them.

*Salmonella typhi* is an encapsulated bacterium and vaccination with the Typhim Vi™ polysaccharide vaccine can induce an antibody response in a controlled setting. Recently, a *Salmonella typhi* Vi IgG ELISA that can measure the antibody response has become available. So far, ASI has not been performed for the indication of distal pancreatectomy in an elective setting, whereas, this population might benefit even more as they are less likely to develop spontaneous splenosis due to posttraumatic seeding. In the present study, we aim to assess the splenic immune function after ASI performed during minimally invasive (laparoscopic or robotic) DPS as compared to minimally invasive DPS without ASI.

## Methods

### Study design

The study is an international multicentre, open-label, randomized controlled trial with parallel groups. Patients are randomized to the intervention (ASI) or control group (splenectomy) at two possible time points: prior to or during surgery. The patients in the control arm are presumed to have no splenic function. In addition, a third group, namely minimally invasive spleen-preserving distal pancreatectomy (SPDP), serves as a control with the assumed normal function of the spleen. The participants will be followed for 7 months and the study will be conducted over a 2-year period. Patients are recruited in six study sites with considerable expertise and a high annual volume in hepato-pancreatico-biliary surgery: The University Hospital Southampton; University Hospitals Birmingham; Morriston Hospital, Swansea (all in the UK); Fondazione Poliambulanza Istituto Ospedaliero in Brescia, Italy; Virginia Mason Medical Center, Seattle; and the Miami Cancer Institute, Miami (both USA).

### Participants

All patients undergoing pancreatic surgery are discussed in a multi-disciplinary team (MDT) meeting. Prior to the MDT, a recent abdominal CT scan, an MRI and/or endoscopic ultrasound (EUS) are executed for the diagnosis and to determine the surgical approach (either minimally invasive DPS or SPDP) (Fig. 1).

**Fig. 1 Fig1:**
[figure not shown]
Trial flowchart. ASI, autogenic splenic implantation; DPS, distal pancreatectomy with splenectomy; SPDP, spleen-preserving distal pancreatectomy

The inclusion criteria for this study are as follows: (1) patients are scheduled for elective minimally invasive DP with or without spleen preservation for suspected benign or low-grade malignant lesions (including low-grade neuroendocrine tumours) of the pancreatic body or tail; (2) patients must be fit to undergo distal pancreatectomy (American Society of Anaesthesiologists (ASA) classification ≤ 3) and (3) patients are at least 18 years old. Exclusion criteria comprise (1) proven or suspected pancreatic ductal adenocarcinoma; (2) asplenia (either functional, surgical or congenital); (3) any other known immune deficiency disorder; (4) known allergy to any of the Typhim Vi™ polysaccharide vaccine containing components; (5) pregnancy; and (6) lacking capacity to consent. If any of the exclusion criteria apply, the patients will be deemed not eligible for participation. Potential participants, who meet inclusion criteria, are approached by their treating surgeon during their outpatient visit. If the potential participant is interested in participating, a local researcher will further explain the trial in depth. Participants are offered at least 24 h to decide and consider informed consent (Fig. 2).

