### Primary outcome

The primary outcome is the clearance of polysaccharide encapsulated bacteria measured by titres of *Salmonella typhi*-specific antibodies just prior to vaccination 6 months after surgery and 4 to 6 weeks thereafter.

One 6-mL serum tube will be used for sample collection immediately prior to vaccination with Typhim Vi™. Pre-vaccination-specific antibody levels will be determined. The vaccine (Typhim Vi™, Sanofi Pasteur MSD) will be given immediately after taking baseline blood. The procedure for the second measurement of *Salmonella typhi*-specific antibody response is identical to the first one. Pre- and post-immunization serum samples are separated by centrifugation and subsequently stored in aliquots at ≤  − 20 °C until analysis. All samples will be shipped to the University Hospital Southampton and simultaneous performance of specific antibody testing will be carried out in the University Hospital Southampton after the last patient completes the 7-month follow-up period.

*Salmonella typhi*-specific antibodies are measured using a commercially available ELISA kit (VaccZyme™ Anti-S. typhi Vi human IgG EIA from The Binding Site Group Ltd., Birmingham, UK). Samples are run in duplicate following manufacturer instructions. The results of specific antibody levels to Typhim Vi™ are expressed as U/mL (normal range, 7.4–600 U/mL). The value of the response is given as the ratio between pre- and post-immunization antibody levels. A threefold increase between titres pre- and post-vaccination will be used to define a normal antibody response according to prior literature [31, 32]. Participants are advised not to have any other vaccinations during the study period.

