## Discussion

Sequelae of splenectomy can be devastating and lethal [3, 4]. Whenever possible, splenic preservation after trauma or elective abdominal surgery should be attempted [20]. If splenic preservation cannot be achieved, the only potential way to preserve splenic function is ASI. Several centres have published case series of ASI in trauma patients, showing their positive experience in terms of safety and feasibility [23, 34]. However, splenic function measurements have not been carried out extensively and there is a lack of standardized reporting on how to measure the function of the spleen [26, 35, 36]. Mimicking an infection caused by encapsulated bacteria through vaccination, followed by measuring the specific antibody response, seems the most realistic surrogate outcome to assess splenic immune function. In this randomized trial, we assess splenic immune function using immunoglobulin count in response to a *Salmonella typhi* vaccination. The Typhim Vi™ polysaccharide vaccine was chosen over the non-conjugated Pneumovax 23® because of cross-reacting and different immunogenicity towards different serotypes and high pneumococcal pre-immunization levels in the population have been described, Whereas, the level of endemic infection with *Salmonella typhi*is lower [37, 38]. The newly developed *Salmonella typhi*Vi IgG ELISA measures the response to the Typhim Vi™ polysaccharide vaccine and allows quantifying the specific production of antibodies in response to the vaccination with higher power for discrimination than the Pneumovax 23® [29].

The decision to include only patients who are allocated to undergo minimally invasive surgery was made based on the following rationale: every surgery is an insult to the human body and, therefore, generates an inflammatory response. It has been suggested by several studies that the minimally invasive approach initiates less of an inflammatory response as compared to the open approach [39–42]. Hence, we felt that including only patients who will have minimally invasive surgery creates a more homogeneous study population and a fairer comparison.

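### Earlier typhoid vaccination or infection is not an exclusion, and the threefold rule uses the baseline titre only as a denominator, so prior exposure can dilute the ASI v DPS comparison

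*Protocol article*

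**What the plan says.** The Participants section of the protocol article gives a closed list of six exclusion criteria. Two bear on the immune test besides asplenia: "any other known immune deficiency disorder" and "known allergy to any of the Typhim Vi™ polysaccharide vaccine containing components". Neither covers earlier typhoid vaccination or infection.

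The Primary outcome section has blood taken immediately before the vaccine is given at 6 months: "Pre-vaccination-specific antibody levels will be determined". It then states "The value of the response is given as the ratio between pre- and post-immunization antibody levels" and "A threefold increase between titres pre- and post-vaccination will be used to define a normal antibody response". No rule is given for a patient whose starting titre is already high. The one restriction on vaccination looks forward only: "Participants are advised not to have any other vaccinations during the study period".

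The Statistical analysis section compares categorical outcomes with unadjusted chi-square or Fisher tests, includes every randomised patient with a titre, and plans no subgroup analyses.

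The Discussion explains the choice of vaccine. One reason for not using the pneumococcal vaccine is that "high pneumococcal pre-immunization levels in the population have been described". Typhim Vi is preferred because endemic typhoid infection is less common.

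**The concern.** The authors recognise that pre-existing antibody can spoil a vaccine-response test, and they chose the vaccine partly for that reason. Their argument covers natural infection only. Adults at UK, Italian and US sites may have had a Vi vaccine before, for example for travel, and nothing in the eligibility list or the vaccination advice reaches back to that.

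A fold-rise rule does not neutralise a high starting titre. The larger the denominator, the larger the post-vaccination titre must be. A previously exposed patient can therefore be counted as a non-responder for a reason unrelated to the spleen.

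The design has little room for such patients. The sample size calculation assumes 99.9% response in the ASI arm, which leaves 0.1% for non-response from all other causes. The same patients in the SPDP group would make the reference for normal function look abnormal.

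**Working it through.** **Inputs from the Sample size calculation section.** Response 99.9% (ASI) and 40.3% (DPS), 80% power, 5% significance, 12 evaluable and 15 randomised per arm. The Statistical analysis section makes the test two-sided.

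**Reproducing the plan's figure.** With p1 = 0.999, p2 = 0.403, difference d = 0.596 and mean p = 0.701:

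- n = [1.960·√(2·0.701·0.299) + 0.842·√(0.999·0.001 + 0.403·0.597)]² / 0.596² = (1.269 + 0.414)² / 0.355 ≈ 7.97, so 8 per arm.
- With continuity correction: (n/4)·[1 + √(1 + 4/(n·d))]² ≈ 11.1, so 12 per arm, as stated.
- 12 / (1 − 0.20) = 15, so the randomised number allows for 20% dropout.
- Exact Fisher power at 12 per arm, by enumeration of all tables, is 93.7%.

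**Adding prior exposure.** Let q be the share previously exposed and r the share of those who reach threefold whatever their spleen does. Neither is in the document; both are assumed.

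- ASI rate = (1 − q)·0.999 + q·r
- DPS rate = (1 − q)·0.403 + q·r
- Difference = (1 − q)·0.596

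Example, q = 10% and r = 30%: ASI = 0.8991 + 0.03 = 92.9%; DPS = 0.3627 + 0.03 = 39.3%; difference 53.6 points instead of 59.6; Fisher power at 12 per arm 73.5%.

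Fisher power for r from 10% to 50%:

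| q | 12 per arm | 15 per arm, all evaluable |
|---|---|---|
| 0 | 93.7% | 98.9% |
| 5% | 81.5-84.8% | 90.9-93.9% |
| 10% | 71.8-75.9% | 81.3-86.8% |
| 20% | 56.0-58.9% | 63.2-69.4% |

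**A milder assumption.** If exposed patients respond at half the usual rate of their own arm, both rates are multiplied by (1 − q/2). Power at 12 per arm is then 86.8%, 80.9% and 71.2% at q = 5, 10 and 20%.

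**Chance imbalance.** With 12 per arm and exposure independent of arm, the probability that the arms differ by two or more exposed patients is 29% at q = 10% and 44% at q = 20%. At q = 5%, the probability of at least one exposed patient among 24 is 1 − 0.95²⁴ = 71%.

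**Assay range.** The kit's range is given as "normal range, 7.4–600 U/mL". If 600 were also the upper measuring limit, which the document does not say, a starting titre above 600/3 = 200 U/mL could not show a threefold rise without further dilution.

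**The case against.** A reader might infer that prior exposure biases the ASI v DPS comparison. The documents do not support that. Allocation is randomised 1:1 and the exposure precedes surgery, so it is balanced in expectation; what remains is dilution and chance imbalance. Only the SPDP group is outside that protection.

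A reader might also infer that baseline antibody is ignored. It is measured in every patient and forms the denominator of the ratio. The accurate statement is that it enters in no other way, and that a ratio does not remove the effect of a high start. Infection was considered too, in the choice of vaccine; earlier vaccination was not.

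The strongest objection is to the size. Both q and r are assumed. The model gives exposed patients no treatment effect at all, and at r = 50% exposed DPS patients would respond more often than the 40.3% assumed for unexposed ones. The losses start from 94%, whereas the plan aimed for 80%. Power stays above 80% at q = 5%, and also at q = 10% if all 15 per arm are evaluable. If the healthy persons behind the 99.9% included people already exposed, part of the effect would be counted twice; that source is not shown. All of this stands, and it makes the point minor.

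An added sensitivity analysis could be left to an SAP. The eligibility list could not: it is fixed in this document and is silent on earlier exposure.

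**Conclusion.** The gap is real but minor. The exclusion list omits earlier typhoid Vi vaccination and known infection, and under the threefold rule a high starting titre can turn a patient with working splenic tissue into a non-responder. The cost to the randomised comparison is power and precision. The loss is serious only if exposure is fairly common: on the stated assumptions, power at 12 evaluable per arm falls below the planned 80% somewhere between 5% and 10% exposed, and to under 60% at 20%. With 15 evaluable per arm, 10% exposure is tolerable. The true share is unknown, so these figures show sensitivity; they do not show that the trial is underpowered. The SPDP group's role as the normal reference is more exposed, because no randomisation balances it against the other two groups.

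**What to change.** 1. For patients still to be enrolled, add earlier typhoid vaccination or known typhoid infection to the exclusion criteria. The Trial status section expects recruitment to end in May 2023, so this may reach few patients.
2. For patients already enrolled, including the SPDP group, record this history before the titres are assayed, from vaccination or medical records where possible rather than recall.
3. Before the assay, pre-specify a supportive ASI v DPS analysis of log post-vaccination titre adjusted for log pre-vaccination titre, and a sensitivity analysis of the threefold endpoint without patients with documented earlier exposure.

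The timing allows this: all samples are tested together after the last 7-month visit, so the analyses can be fixed before any result exists.

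The cost is one eligibility line, one case report form item and two short analyses. The downsides are a few candidates lost, a slightly smaller sensitivity set and some mixing of eligibility rules within the trial. History would be partly ascertained after randomisation in an open-label trial, which is why records are preferable. The pre-vaccination titre is itself drawn 6 months after surgery, so the adjusted analysis should stay supportive and not replace the primary comparison.

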**Fig. 2 Fig2:**
[figure not shown]
Schedule of enrolment, intervention and assessments. *If SPDP cannot be achieved, patients will be randomized to DPS with or without ASI

Routine preoperative blood samples are obtained for baseline analysis and fitness to undergo laparoscopic DP is assessed by an anaesthesiologist. In the case of a planned minimally invasive DPS, all patients will receive pneumococcal vaccination, *Haemophilus influenzae *type b conjugate vaccine and meningococcal conjugate vaccine according to national guidelines prior to or after surgery [7].

